### **Coupon**

Each coupon will be uniquely coded in order to link seeds with new individuals in their recruitment chain. Each coupon will have an identifying code of the recruiter and a unique code for new recruitments, allowing us to

track social networks. Names and other personal identifying information will not be collected on any of the study forms. The coupons will be produced in such a way as to make them difficult to reproduce.

The coupon will consist of two parts and each part will bear an identical recruiter code. When the recruiters invite a new person they must hand over one of the parts of the coupon to the new recruited person, with the other part being kept by the recruiter. When the recruiters come back for their incentives, they must hand over their half of the coupon, which must match the half handed out to the new participants. In this manner the participants will remain anonymous, no names or personal identifying information will be collected on any study form.

Coupons will have the following elements:

- ID number (coupon number)
- Survey name (the target population and exact purpose will not be mentioned)
- Interview site address
- Telephone number of interview site
- Days and hours of operation
- Activation date: Date before which the coupon may not be used for enrolment. This date may vary; initially, the activation date will be two days after the coupon's issuance date. At the discretion of the study coordinator or the PI, recruits presenting coupons before the activation date may be accepted.
- Expiration date: Date after which coupon should not be used. Initially, coupons will be valid for two weeks. This time period may be extended or shortened if coupon return rates are below or above expectation and as the sample size approaches the target. At the discretion of the study coordinator or the PI, recruits with coupons that are within a set period of days past the expiration date may still be accepted.
- Information about its use and validity

A coupon may be invalid if: expired, tampered with, unreadable, or already used. Invalid coupons will be retained and stamped "VOID." Valid coupons of recruits undergoing screening for eligibility will be retained and stamped "USED." Recruits who are re-scheduled for a future visit will have their coupons returned to them. Re-scheduled visit dates may be past the coupon expiration date without rendering the coupon invalid.

### ***Incentives***

MSM, transgender women and female sex workers that participate in the peer referral study (RDS), whether they are the initial "seeds" or a subsequent recruit, will receive mobile phone credit or other gift worth 900 Angolan Kwanzas (9 USD). The participant must consent to completing the survey and undergoing HIV and STI testing in order to be eligible for any amount of the incentive. If they subsequently refuse the HIV test and/or do not complete a majority of the questionnaire, they will not receive any incentive.

If an RDS participant successfully recruits one additional person to participate, they will receive an additional mobile phone credit or other gift worth 400 Angolan Kwanzas (4 USD) beyond the primary incentive, for a total incentive worth 1300 Kwanzas (~13 USD). If s/he recruits two additional persons to participate, s/he will receive an additional phone credit or gift worth 800 Kwanzas beyond the primary incentive, for a total incentive of 1700 Kwanzas (~17 USD). If s/he recruits three additional persons to participate, he will receive an

additional 1200 Angolan Kwanzas (~12 USD) beyond the primary incentive, for a total of 2100 Kwanzas (~21 USD).

### **Collection of biologic specimens and testing**

All participants will be tested for HIV using a rapid test through finger prick blood sample at the health center study site. Participants will be offered syphilis, Hepatitis B, and Hepatitis C testing based on the SADC protocol. Nurses will collect venous blood for STI testing and provide results when participants return to the study site on a later date.

### **E. Sample Size**

The sample size will be calculated based on the budget and the estimated number of sex workers, men who have sex with men and transgender women that are thought to be reachable (Table 3). For PLACE/Programmatic mapping the exact number of each population interviewed will depend on the site identification, verification and patron and worker interview steps.

Approximately 2000 men and women will be interviewed and tested for HIV at venues in Luanda. We expect to recruit approximately 600 sex workers, 600 men who have sex with men and 200 transgender women. Around 600 participants could be from the general population. Approximately 400 female sex workers will be recruited in Cabinda using RDS.

**Table 3 Summary of interviews to be completed by province**

| Population                                      | Luanda | Benguela | Bié | Cunene | Cabinda | Total |
|-------------------------------------------------|--------|----------|-----|--------|---------|-------|
| Community informant interviews                  | 500    | 500      | 500 | 500    | 0       | 2000  |
| Venue informant interviews                      | 700†   | 500      | 500 | 500    | 0       | 1500  |
| Behavioral interview and HIV/STI testing |        |          |     |        |         |       |
| Female sex workers                              | 600    | 400      | 400 | 400    | 400     | 2200  |
| Men who have sex with men                       | 600    | 400      | 400 | 400    | 0       | 1800  |
| Transgender women                               | 200*   | ‡        | ‡   | ‡      | 0       | 200*  |
| Other men and women at venues                   | ‡      | ‡        | ‡   | ‡      | 0       | ‡     |

\* Could be less based on the number and percent of people at venues who identify as transgender, has received money for sex and who are men who have had sex with a man in past 12 months. † If there are more than 700 venues are identified in Luanda, a sample of venues will be selected. \*\*The sample must be confirmed by UNC staff prior to field work. \*\* ‡ No defined sample size as sample will depend on distribution of key populations in venues sampled.

## ***F. Population Size Estimation Procedures***

### ***PLACE-Programmatic Mapping Population Size Procedures***

The process is to estimate the number of each type of key population at each site, sum up the estimates across all of the sites, adjust the estimate to take into account visits to multiple sites and mobility, and finally extrapolate the number to areas not covered by the mapping.

### ***RDS Population Size Procedures***

We will use the unique object multiplier method to obtain a population size estimate of female sex workers in the province of Cabinda. The multiplier method is the most commonly used population size estimation method, in part because it is relatively straightforward and utilizes simple calculations. The unique object multiplier method involves the distribution of a set number of unique objects, such as key chains, to members of the target population. Unique objects will be distributed widely at specific locations where female sex workers congregate (i.e. bars, brothels, hotels, etc.). The goal is to distribute as many unique objects as possible, but no less than the agreed upon study sample size.

#### ***Data Sources***

This method uses data from two overlapping sources to estimate population size. The first set of data comes from the number of unique objects distributed in a two week period by field staff two weeks preceding the implementation of the RDS survey. The second set of data comes from the RDS survey data, where study participants are asked whether they had received a unique object. The number of participants receiving a unique object is then multiplied by the inverse proportion of the percentage of RDS participants who received the unique object.

Source 1: Field staff distributing unique objects will report data regarding location and time of unique object distribution, and the exact number of unique objects distributed using the Population Size Estimation Form (Appendix 12).

Source 2: Relevant questions related to receipt of unique objects will be included in the RDS survey. These include:

1. Did you receive a [object] when contacted by a field staff in the past few months?
2. Can you show it to me?
3. Can you describe it to me? (if the [object] is described properly, show it to them)
4. Is this the [object] you received?
5. How many [objects] did you receive?
6. When did you receive this [object]?
7. Where did you receive this [object] (at what site)?

### *Data Collection*

A standardized form (Appendix 12) will be used to collect data from staff distributing unique objects two weeks prior to the implementation of the RDS survey. Data will include a) Number of unique objects distributed to eligible female sex workers, b) Location of unique object distribution; and c) Time of unique object distribution.

### *Sample Size*

The number of unique objects will be agreed upon by the project coordinator and organizations assisting in distribution. While increasing the number of unique objects may improve precision of the final estimate, there is no set formula to determine a specific number for distribution. Factors related to distribution of unique objects, such as logistics and human resources, will be considered. In general, the number of unique objects will be determined by the number of contacts the distributing organizations anticipate reaching within one to two weeks. The process for determining the sample size will be documented and included in study reports. The distribution of unique objects should saturate the target population so that by the end of the distribution period all people meeting the study definition in the study are have received the unique object.

### *Implementation*

NGOs and other organizations will be asked to distribute a specified number of unique objects to female sex workers for a period of two weeks. Each person will receive only one object and will be asked to keep the object because they may be asked about it by another field staff in the near future. Field staff will determine whether the participant has previously received a unique object to avoid double counting. No personal identifying information will be collected.

To estimate population proportions, persons enrolled in survey will be asked if they had received the unique object and be asked to show or describe the object to the interviewer. Those who are in possession of the object or can recall it in sufficient detail will be counted as the proportion who received the unique object. Calculations are then made to estimate the population size.

### ***G. Selection and Training of the Field Team***

All members of the field team will be contracted locally. The Project Coordinator overseeing both RDS and PLACE studies will be the first field staff member to be selected and will participate in the selection process of other field staff members. The study field coordinator for each province will be interviewed by the project coordinator and study investigators. Potential interviewers and receptionists will be interviewed by the project and field coordinators.

All members of the field team will be trained in the following:

- Introduction to RDS methodology (RDS team only)
- Introduction to PLACE methodology (PLACE team only)
- Study procedures and flow

- Interview techniques on how to obtain answers to sensitive and non-sensitive questions
- Data collection instruments
- Management of electronic instruments for data collection
- Ethical aspects involving human research
- Stigma and discrimination issues affecting MSM, female sex workers and transgender women
- Communication skills
- Confidentiality
- Data security

Theoretical and hands-on training will be conducted by study investigators and national and international consultants. During data collection, each field team will receive direct supervision by one of the study investigators to troubleshoot specific recruitment and data collection procedures and to anticipate and solve potential problems that might arise in the field.

Interviewers and supervisors will be provided specialized training on the questionnaire, the use of the smartphones and survey software, and interviewing procedures.

Specialized HIV counselors trained in and responsible for providing information about HIV and other STI, the HIV test, and where people can go for additional HIV services.

Nurses will conduct HIV, syphilis and Hepatitis B rapid testing at or near the study site.

Laboratory personnel: will process the VDRL or RPR, N. gonorrhoeae, C. trachomatis and viral load tests the study laboratory, deliver the results of the tests to the participants as they return for their results, and will also store, coordinate adequate transport, and prepare the samples.

Study staff, including supervisors, interviewers, nurses, volunteers and laboratory personnel will be provided a special training by MOH and UNC staff in order to carry out the study protocol and comply with study procedures. In addition, counselors, who will be selected from a pool of experienced, trained personnel from the MOH, will be provided a refresher training course on counseling skills and provided detailed information on how to refer patients found to be HIV- infected and on partner notification practices. All personnel working on the study will be provided special training on keeping information confidential. Experienced research, program and laboratory staff from the MOH and UNC will conduct the training.

Recruiters (interviewers and volunteers) and supervisors will be provided training on RDS recruitment methodology. RDS uses the practice of participant-driven recruitment and offers remuneration to participants who refer their peers to study sites. Interviewers and volunteers will be in charge of instructing the participants on the eligibility criteria, how to recruit other participants using coupons and the reimbursement for participation.

Laboratory staff and nurses will be given specialized training on the rapid HIV, syphilis, Hepatitis B and CD4 test, venipuncture and collection of blood, handling of urine specimens, vaginal and anal swabs. Laboratory technicians will be given specialized training on processing, storage, and transport of urine specimens, vaginal and anal swabs and venous blood for viral load testing. They will also receive refresher training on biosafety

and protocols they should use in the event of unexpected occupational exposure to blood or blood products. Training will include provision of a laboratory handling procedures manual.

## **VII. DATA MANAGEMENT**

### ***A. Data Management***

Data will be collected using a smartphones to minimize data entry error. Electronic versions of the survey will be created by Tchikos and pre-tested for accuracy and relevance. Upon completion of the interview, the interviewer will press a "submit" button, which encrypts the data before sending it to a secure server in Angola, specified for data storage. This server is only accessible by the server manager and key study staff, and is password protected. When internet access is unavailable for submitting completed surveys directly to the server, interviewers will save the data on the smartphone until the end of the work day, at which time the tablet will be returned to the field supervisor or study coordinator. The field supervisor or coordinator will then download the data from all smartphones onto a password protected laptop or desktop. When internet access is restored, he or she will send the encrypted data to the server.

Data will be stored in a database generated by the software and transferred weekly via a secure FTP server managed by UNC or data download to UNC. Separate databases will be created for each survey and will contain data from the questionnaire for all participants. Data will be backed up daily and the data manager will run weekly cleaning and validation programs and provide feedback to the field to carry out appropriate corrective actions. These will include checking for screening criteria, incomplete interviews, and proportion of missing key variables. All data collected on smartphones will be stored on a secure server. Once the data collection phase is completed, data will be transferred to SPSS, SAS and RDSAT for analysis. The clean data sets will be moved by authorized personnel for long-term storage on UNC's secure server. Only members of the UNC research team for this study that are using the data will have access to the related data files on that secure server.

Only authorized, survey-related personnel will have access to any data, whether computerized or in hard copy. Electronic data will be stored in a password-protected computer in the study's coordinator's locked office. Hard copy and back-up disks will be stored in locked file cabinets. Databases containing study information, hard copy files, and consent forms will be destroyed five years after the completion of the survey. The data will be joint property of UNC and the INLS. Records and data will be maintained based on their recommendations and regulations. As per the separate data use agreement cleaned data sets will be transferred to the Dataverse at UNC's Odum Institute. Appropriate precautions will be taken to protect against indirect identification of individuals. People who wish to obtain the data will have to complete a request explained their intended purpose for the data.

### ***B. Coupon Data Management***

RDS coupon data will be managed using a coupon management software and stored into a database. This software will allow field staff to monitor participants, assign coupon ID numbers, verify study eligibility, track study participation, track number of incentives given out, monitor recruitment chain growth in real-time, and back up data. This database will contain the coupon number of each participant recruited, and coupon numbers provided to participants for peer recruitment.

### ***C. Population Size Estimation Data Management in Cabinda***

Field staff will complete a form recording the site (by site code), time, and number of unique objects distributed. After field correction, forms will be faxed, e-mailed, or hand-delivered to the data manager, who will double-enter the data into a password-protected Microsoft Excel spreadsheet stored centrally at a site designated Tchikos. All data will be encrypted before being transferred via secure FTP server and will be backed up daily.

### ***D. Study Identification Numbers***

For RDS, a unique RDS code will be assigned to all participants. The RDS code will be noted in the survey coupons and entered twice in control coded fields in smartphone. Each coupon will have a unique coupon number for new recruitments and will be numbered in such a way as to allow the coupon management system to track social networks.

For PLACE, a unique PLACE code will be assigned to all participants. This code will come from the specimen identification stickers. We will use the same PLACE code on all study forms, including test results form, questionnaire and specimens collected. The unique code will guarantee that all records for a participant can be reliably linked to one another. In the smartphone questionnaire, the PLACE code will be entered twice in control coded fields to detect any errors.

All participants will also be assigned a unique identifier code using a combination of gender, year of birth, day of birth, and the first two letters of their parents' given name. The unique identifier code will be piloted for acceptability as part of the mapping readiness assessment. The unique identifier code will be constructed by the nurse or counselor conducting HIV testing and entered on the test results record. This unique identifier code will allow participant to retrieve their STI or viral load test results if they have lost their unique RDS or PLACE code card. It will also allow for piloting a unique identifier code that could be used by outreach workers to avoid double-counting people reached during prevention activities.

### ***E. Data Quality Control***

The field coordinator will be responsible for the flow of information and the quality control of the information flow between the venues, study site in Cabinda and the Tchikos.

Data quality control will begin in the pre-test phase, with the identification and replacement of unclear survey terms and questions. The second step in data quality control will occur during training of field staff, especially of interviewers who will be trained to ask personal and sensitive questions in a non-judgmental manner. The third step in data quality control will entail local and continuous monitoring of recruitment activities, protection of participant's rights, data collection, coupon management, and overall compliance with the protocol.

## **VIII. Data Analysis**

### ***A. RDS Analysis***

RDS-based surveys will be analyzed with RDSAT or RDS-A, free software packages that adjust RDS-collected data for network sizes and recruitment patterns. Using RDSAT and NetDraw, a software for drawing social

networks, we will examine the equilibrium of key variables and recruitment patterns by key demographic characteristics to identify potential biases associated with recruitment (i.e. homophily, number of recruitment chains). We will exclude all data from seeds in the analysis and export RDSAT weights directly into SAS to conduct analyses not supported by RDSAT. We will also use RDSAT to generate population estimates for specific key indicators from UNAIDS and PEPFAR^2 for behavioral surveillance purposes (Table 4).

### **B. PLACE Analysis**

PLACE-based surveys will be analyzed using survey specific commands in SAS to account for the cluster design and weights. Weights will be constructed to produce unbiased population-based estimates and will be based on the following information: attendance at venues, attendance at specific venues or cluster size. Non-response bias will also be assessed by comparing proportion of missing data by key characteristics. We will generate population estimates for specific key indicators (Table 4).

One study objective is to estimate the proportion of key populations at each step of the HIV testing and treatment cascade, the basis for the LINKAGES Project. Table 4 includes indicators for the percent of HIV positive people who are aware of their status, the percent of those positive that are enrolled in HIV care, the percent who have initiated ART, the percent sustained on treatment for 12 months and the percent who are virally suppressed. Other indicators focus on coverage of HIV prevention activities such as HIV testing, STI screening, condom and lubricant distribution, information on HIV, AIDS, STI and safe sex and the percent of the population that has received a package of interventions.

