### **Rationale:**

The complexities of engagement in HIV care and treatment are well-identified in sub-Saharan Africa. Female sex workers, men who have sex with men and transgender women are susceptible to these complexities, while facing additional individual level barriers. LINKAGES will use the HIV Services Cascade as the overall strategic

framework for the project. The HIV cascade illustrates how individuals should ideally move through the continuum of HIV prevention, care, and treatment services to reduce HIV transmission as well as to ensure a high quality of life for key populations living with HIV. Use of the HIV cascade and the enhanced use of programmatic data associated with the cascade will allow the Ministry of Health and civil society organizations to identify “leaks” in the system where key populations are lost to follow-up or unable to access critical services in the comprehensive package such as HIV testing and counseling, sexually transmitted infection screening and treatment and other HIV services including enrollment on antiretroviral therapy. The WHO has recently released recommended global guidance on HIV prevention and treatment which includes an emphasis on key populations. The proposed work will align with the WHO guidance.

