| Initiate on ART | Proportion of key populations currently receiving antiretroviral therapy (TX_CURR/CUSTOM INDICATOR)                                                         | PMP 1.12b        | Num: Number of people with HIV who are taking ART

Denom: Number of people diagnosed with HIV                                                                                                             |
|                 | Proportion of key populations currently receiving antiretroviral therapy among those who are currently enrolled in care

(TX_CURR/WHO 1.5 & WHO 1.3 & ART-2) | PMP 1.13         | Num: Number of people with HIV who are taking ART

Denom: Total number of key populations who tested positive for HIV, know their results and are currently enrolled in care                              |
| Sustain on ART  | Proportion of key populations known to be alive and on treatment 12 months after initiation of antiretroviral therapy (TXT_RE/WHO 1.6)                             | PMP 1.14b        | Num: Number of people with HIV who are taking ART for at least 12 months

Denom: Number of people diagnosed with HIV                                                                                      |
|                 | Percent of key populations with HIV known to be on treatment 12 months after initiation of antiretroviral therapy (TX_RET)                                         | PMP 1.15
Core | Num: Number of people with HIV who are taking ART for at least 12 months

Denom: Number of key populations in the ART start-up group initiating ART at 12 months prior to the end of the reporting period |

Programmatic Mapping and HIV/STI Prevalence Study among Key Populations in Angola

| Cascade Step        | Indicator                                                                                                                            | Indicator #      | Measure                                                                                                                                                                                                                   |

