| C23        | In the past 12 months, have you received information about HIV or AIDS from any health worker?                                                                                                   | Yes
1                                        | No
2     |
| C24        | Are you currently seeing a health worker for an HIV infection?                                                                                                                                   | Yes
1                                        | No
2     |
| C25        | Are you currently taking antiretroviral (ART) drugs to treat an HIV infection?                                                                                                                   | Yes
1                                        | No
2     |
| C26        | Now I have a few questions about HIV tests. Have you ever had an HIV test?
IF NO: GO TO C31.                                                                                                  | Yes
1                                        | No
2     |
| C27        | Has a medical provider ever told you that you are infected with HIV, based on an HIV test result? IF NO GO TO C29.                                                                               | Yes
1                                        | No
2     |
| C28        | Think about the first time a medical provider told you that you that you were infected with HIV. Did this occur in the past 3 months? Past 12 months? Or longer ago? IF LONGER AGO, SKIP TO C31. | Past 3 Months
Past 4-12 months
Longer ago | 1
2
3 |
| C29        | Have you been tested for HIV in the past 12 months?
IF NO, GO TO C31.                                                                                                                         | Yes
1                                        | No
2     |
| C30        | IF YES (C29=1) ASK: The last time you were tested, did you get your test result?                                                                                                                 | Yes
1                                        | No
2     |
| C31        | Some people have tried injecting drugs using a needle and syringe. Have you injected any non-prescription drug in the past 12 months?                                                            | Yes
1                                        | No
2     |

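### The plan promises the percent who have initiated ART, but Table 4 and Form C capture current use only, so the PLACE data cannot separate people who stopped ART from people who never started

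*Protocol*

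**What the plan says.** Section VIII.B (PLACE Analysis) ties Table 4 to an explicit aim: "One study objective is to estimate the proportion of key populations at each step of the HIV testing and treatment cascade". It lists what the table contains, including "the percent who have initiated ART, the percent sustained on treatment for 12 months and the percent who are virally suppressed". The Rationale in section IV says what the cascade is for: to find leaks "in the system where key populations are lost to follow-up or unable to access critical services".

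In Table 4, the step *Initiate on ART* has two rows.
- PMP 1.12b is titled as a current-treatment proportion and carries the code TX_CURR. Its denominator is people diagnosed with HIV.
- PMP 1.13 is titled "Proportion of key populations currently receiving antiretroviral therapy among those who are currently enrolled in care".

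Both rows use the same numerator: "Num: Number of people with HIV who are taking ART". No row of the table has a numerator of people who ever started.

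Form C (Appendix 4) has one ART question, C25: "Are you currently taking antiretroviral (ART) drugs to treat an HIV infection". Its one HIV-care question, C24, is also about the present. The form as shown asks nothing about ever having used ART, the start date, the duration or stopping.

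**The concern.** Initiation is a past event and current use is a present state. They agree only if nobody who started has stopped. The text promises the first, and the table puts the second under its label.

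The difference matters because the cascade is meant to distinguish failure to reach a service from loss after reaching it. If people who stopped are counted below the initiation step, part of a retention problem is read as failure to start treatment. The remedies for those two problems differ. The data come from one cross-sectional interview, so whatever Form C does not ask cannot be recovered at analysis.

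**Working it through.** The protocol states no figure for this step, so there is none to reproduce. The check sets the definitions side by side and then sizes the difference under stated assumptions.

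**1. What each place counts, and whether Form C can supply it**

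| Place | Quantity | Needs | Form C source |
|---|---|---|---|
| Section VIII.B text | Ever started ART | Ever-use | None |
| Table 4, *Initiate on ART* (PMP 1.12b, 1.13) | On ART now | Current use | C25 |
| Table 4, *Sustain on ART* (PMP 1.14b) | On ART for 12 months or more, over all diagnosed | Current use and duration | C25 only; no duration |
| Table 4, *Sustain on ART* (PMP 1.15) | On ART for 12 months or more, over those who started 12 months earlier | Start date, including for those who stopped | None |

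**2. How three kinds of diagnosed respondent answer C25**

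- On ART now: yes.
- Started and stopped: no.
- Never started: no.

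The second and third cannot be told apart by any other item on the form.

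**3. Size of the understatement**

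Let *s* be the share of diagnosed people who ever started, and *d* the share of those starters who have stopped.

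- Ever initiated = *s*
- PMP 1.12b = *s* × (1 − *d*)
- Shortfall = *s* × *d*

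Both inputs are assumptions. With *s* = 60%:

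- *d* = 20%: PMP 1.12b = 60 × 0.8 = 48%, a shortfall of 12 points.
- *d* = 40%: PMP 1.12b = 60 × 0.6 = 36%, a shortfall of 24 points.

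Shortfall in percentage points over a wider range:

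| *s* | *d* = 10% | *d* = 20% | *d* = 40% |
|---|---|---|---|
| 40% | 4 | 8 | 16 |
| 60% | 6 | 12 | 24 |
| 80% | 8 | 16 | 32 |

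It is zero only if *d* = 0.

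**4. Whether the next step recovers the loss**

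PMP 1.14b does not. Its denominator is everyone diagnosed, so never starting, stopping, and having started less than 12 months ago all fall into the same gap. PMP 1.15 would recover it, because its denominator is starters, but Form C cannot identify that group. C28 asks how long ago the respondent was first told of the infection. That bounds time on ART for people diagnosed in the past 12 months, but it does not date the start for anyone diagnosed earlier. The 12-month numerator shared by PMP 1.14b and 1.15 therefore has no source on the form either.

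**The case against.** The strongest reply has three parts.

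*The rows are openly about current use.* This stands. Both titles say so, no row labels anyone as never started, and current ART is a legitimate measure of present state in a cross-sectional survey. The rows are not wrong in themselves. The fault lies in placing them under an initiation step and in section VIII.B's description of them.

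*Table 4 does contain a retention measure among starters.* This also stands on paper. A reader might infer that drop-out vanishes from the cascade altogether. The documents do not support that, because PMP 1.15 is defined so as to show it. Table 4 also sets having been enrolled in care (1.6b) against current enrolment (PMP 1.10), which on paper would show a stopper who also left care. What remains is that Form C, with only C24 and C25, can fill neither the starter cohort nor the care contrast.

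*The consequence could be overdrawn.* A reader might infer that programme conclusions would be reversed. The illustration does not bear that out. With 60% ever started, 40% never started and 12–24% dropped out. Failure to start is the largest loss in truth (40) and as shown (52–64). Nor should one calculate a displayed gap between initiating and sustaining. Form C has no duration item, so no such gap could be produced from it.

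**Conclusion.** The mismatch is real. Section VIII.B promises initiation, Table 4 delivers current use, and Form C cannot distinguish stopping from never starting. In the PLACE data the *Initiate on ART* step understates initiation whenever anyone has stopped. The shortfall is 12–24 points if 60% started and 20–40% of them stopped, and 4–32 points over the wider assumed range. These figures illustrate scale only, since the protocol gives no start or stop rates.

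As the form stands, the 12-month rows PMP 1.14b and 1.15 cannot be computed from it, so they do not offset the problem. The prevalence estimates are unaffected. Nothing is concluded about the Cabinda RDS data, because the Appendix 5 questionnaire is not shown.

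**What to change.** **Preferred.**
- Insert two items between C27 and C28: whether the respondent has ever taken ART and, if so, when they started. This position matters. C25 comes before the diagnosis question, whereas the existing skip at C27 already routes people without a reported diagnosis past this point.
- Define *Initiate on ART* as ever started among those previously diagnosed.
- Show PMP 1.12b and 1.13 as a separate *Currently on ART* step. Over the same denominator, ever started minus currently on ART is then the drop-out.
- Use the start date to supply the 12-month rows. An ever/never item alone would not do that.

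**If no items can be added.** Rename the step *Currently on ART*, change section VIII.B to speak of people who are currently on ART, and state that no conclusion on initiation or drop-out will be drawn from the PLACE data. Mark PMP 1.14b and 1.15 as not estimable from Form C.

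**Cost.** The preferred fix takes a few seconds of interview time for diagnosed respondents and adds two self-reported items, with some recall error in the start date. It also means relabelling one Table 4 step. The fallback costs only the rewording, but it gives up the initiation step that section VIII.B promises.
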